#### Sudomotor Autonomic Function Assessment: Sympathetic Skin Response (SSR)

Sympathetic skin response will be evaluated to assess sudomotor autonomic function as previously described [17].

Briefly, the SSR will be measured as change in electrical skin conductance (ESC) following sudden deep inspiration using GSR finger electrodes (MLT118F, ADInstruments, Castle Hill, Australia) at the middle phalanges of the third and fourth fingers of the non-dominant hand during three deep inspirations. Before each measurement of skin electrical conductivity, the measurement system will be calibrated and set to zero. The electrical amplifier (GSR Amp® FE116, ADInstruments, Castle Hill, Australia) to which the electrodes are connected generates a low electrical voltage (22 mV). The current flowing through the skin and the applied electrodes are pre-amplified as an electrical signal by the GSR Amp® FE116 and then transmitted to the PowerLab 4/26® instrument (ADInstruments, Castle Hill, Australia), which converts the acquired analogue skin conductance signals into digital data and allows the subsequent curve display and storage of the data by the LabChart Pro® software package (ADInstruments, Castle Hill, Australia). The subject will perform three sudden deep inspirations at baseline, after each interaction with the instructor during both types of seminars and at the end of class. The SSR value will be computed as the maximum increase in amplitude in ESC after deep inspiration: *SSR = ESC post-inspiration (ESCmax) - ESC Inspiration-Onset (ESCmin)*.

### Neurovascular autonomic function assessment: Laser doppler flowmetry (LDF)

Assessment of dynamic vasoconstriction and vasodilatation of microcirculation following sympathetic stimulation will be performed to evaluate neurovascular autonomic function as previously described [18]. Briefly, assessment will be undertaken using laser Doppler surface probes (INL191 Blood FlowMeter LCC, ADInstruments, Castle Hill, Australia) following deep inspiration to stimulate a vasoconstrictory sympathetic response. The LDF technique utilizes a monochromatic coherent laser source on a fixed cutaneous region. The LDF probe will be attached at the middle phalanx of the fourth finger of the non-dominant hand with a circular strip. Processing and computation of the distribution of frequencies of backscattered light enables an approximation of small vessel blood perfusion. The electrical signal from the LDF probe will be transmitted to the PowerLab 4/26® analogue-to-digital converter (ADInstruments, Castle Hill, Australia), which generates the digitised representation of the microcirculation of the skin. Vasoconstrictory response (VCR) as well as the time required (sec) for the vessel to develop 50% constriction or 50% dilation using Δt50%down and Δt50%up values will be computed [18].

### Pupilomotor autonomic function assessment: Pupil light reflex

Controlled induction of the pupil light reflex can be utilized to evaluate function of both branches of the autonomic nervous system, that is, the sympathetic and the parasympathetic system. While pupil constriction, for example, following a light stimulus, is mediated by contraction of iris sphincter muscle under parasympathetic control, pupil dilation, for example, following arousal or the fight-or-flight response, is induced by the sympathetic dilator muscle. Therefore, pupillary diameters as well as homoeostasis of contraction and relaxation of iris muscles reflecting parasympathetic-sympathetic balances. Measurement of the pupil response to a light stimulus, also referred to as the pupil light reflex, allows separate evaluation of the sudden constriction phase and the subsequent phases of re-dilatation. Dynamic assessment of pupil diameter during these phases allows characterization of parasympathetic and sympathetic responsiveness. Moreover, the reflex is modulated by cognitive factors, including attention, processing of visual input as well as awareness making this test particularly valuable in the comparison of learning methods [19]. Therefore, an automated neuro-optical examination consisting of the dynamic assessment of pupil size and pupil reactivity will be performed using a pupillometer (NeurOptics®NPi®-200 Pupillometer, NeurOptics, Inc., CA, USA) with a sampling frequency 32 Hz and accuracy 0.1 mm as previously described [20]. The pupillary margins will be detected in an automated fashion during infra-red illumination. Margins will be tracked during a five-second period of continuous recording following application of a 154 ms light stimulus at an intensity of 180 μW to induce the pupillary light reflex. Resting pupil diameter, pupil light reflex amplitude and latency as well as recovery time and neurological pupil index (NPi) will be computed. The NPi integrates a series of dynamic pupillary variables including size, latency, constriction velocity and dilation velocity into an algorithm to characterize pupillary responsiveness.

### Experimental seminar

One experimental seminar will be held in two consecutive phases (sessions) comprising a phase of face-to-face on-site teaching and a phase video conference based real-time teaching. Each session will last 40 min with a 10-minute break in-between. Prior to the seminar, participating medical students will be informed about objectives during the seminar by the instructor. A multiple-choice test will be undertaken prior and after each seminar session to assess learning progress with respect to the content of the seminar. The content taught will be selected according to the medical curriculum of the participant’s academic year. It will not be redundant to their previous teaching. The learning objectives/goals of the seminar will be mainly focussed on comprehension, which may include background, integration, and solution. The experimental seminars will be conducted throughout the semester. The lectures included in the study were previously involved in designing multiple-choice questions for student exams and have multiple years of teaching experience. However, it cannot be excluded that students had attended previous classes of the instructors delivering the experimental seminars.

#### Learning progress test

Three qualified lecturers, who either hold a professorship or doctorate degree and have multiple years of teaching experience, will provide 10 multiple-choice questions according to seminar’s content including knowledge, problem-based and composite questions. Each multiple-choice question will have five different options with only one correct option. For each seminar session, five identical questions will be handed out to the participating subjects as pre- and post-tests. These tests will be given to students before and after each seminar session. The achieved score after each seminar session will be compared with the score achieved before the seminar begins to reflect the learning success.

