We aim to characterize the effects of traditional on-site versus videoconference-based education on the autonomic nervous system in medical students and to determine whether changes in autonomic functions during the two seminar forms translate into differences in learning success and stress levels.

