### Statistical analysis plan

The primary endpoint constitutes a group difference in Standard Deviation of all NN intervals (SDNN). Further endpoints encompass a change of remainder functional parameters of the ANS. The study is conceptualized as a pilot study due to lack of preliminary work. Because of the exploratory nature of this study and absent preliminary research using the same assessment techniques we did not undertake a formal sample size calculation. We intend to allocate 48 subjects (*n* = 48) as targeted sample size.

All statistical calculations will be performed using GraphPad Inplot, ISI software and PRISM Version 5.01 (Graphpad Holdings, LLC, CA, USA). Normality will be assessed by descriptive and analytic methods (Shapiro–Wilk test). Under crossover conditions randomization with a two-period, two-treatment design (2 × 2 design) will be performed. In addition, carryover effects between treatments and periods will be tested using two-way repeated measures ANOVA (mixed model). A two-sided *p* > .05 indicates no carryover effects due to sequencing order. Measured values at each treatment period will then be normalized by mean measured values at baseline. Data include HRV parameters (RMSSD, SDNN, VLF, HF, LF, LF/HF, total power), sudomotor parameters (SCL, SSR), neurovascular function parameters (Δt50%down, Δt50%up, VCR), and pupil dynamics (resting pupil diameter, pupil light reflex amplitude and latency, recovery time, NPi). Between-group differences (baseline vs face-to-face vs videoconference) will be determined using one-way analysis of variance ANOVA followed by Student–Newman–Keul test. Not normally distributed data will be analysed either after log-transformation or *via* non-parametric Friedman two-way ANOVA approach. The significance level is set to alpha = 0.05 and two-sided *p* < .05 is considered significant.

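### Five questions per session resolve only a difference in learning gain of about 0.7 to 0.9 question in 48 students; adjusting the post-test for the pre-test is a free improvement, and a null result should not be read as equal learning

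*Protocol article*

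**What the plan says.** The aim, at the end of the Introduction, is to characterise autonomic effects of the two teaching forms and "to determine whether changes in autonomic functions during the two seminar forms translate into differences in learning success and stress levels". Learning is therefore one side of the question, although the Statistical analysis plan section names SDNN as the primary endpoint.

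The Learning progress test section sets the instrument. Three lecturers "will provide 10 multiple-choice questions according to seminar’s content including knowledge, problem-based and composite questions". These are split by session: "For each seminar session, five identical questions will be handed out to the participating subjects as pre- and post-tests". On format: "Each multiple-choice question will have five different options with only one correct option". On scoring: "The achieved score after each seminar session will be compared with the score achieved before the seminar begins to reflect the learning success".

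The comparison is within student: "Under crossover conditions randomization with a two-period, two-treatment design (2 × 2 design) will be performed". On size: "We intend to allocate 48 subjects (*n* = 48) as targeted sample size". On testing: "The significance level is set to alpha = 0.05 and two-sided *p* < .05 is considered significant". The same section calls the study an exploratory pilot without a formal sample size calculation. Limitations and strengths discloses that the learning test will not be validated, and relies on the crossover to reduce variability between individuals.

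**The concern.** A change in a 0-5 score is a coarse measure. The crossover cancels stable differences between students. It does not cancel the chance element in which of five items a student gets right, including lucky guesses. That noise enters each student's contrast four times: before and after, in each of two sessions. The disclosed limitation covers validation, not test length or guessing.

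Two uses of the score are at stake. If the settings do not differ significantly, a reader may conclude that videoconference teaching is as effective, when the test could have missed a moderate difference. And if the learning contrast is mostly noise, its correlation with autonomic change shrinks towards zero whatever the true relation.

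**Working it through.** The article gives no power, SD or effect size for learning, so there is no stated figure to reproduce.

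**Inputs from the article:** k = 5 items per session, five options each (chance rate 1/5), 48 students each in both settings, two-sided alpha 0.05.

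**Assumptions:** 80% power; items independent; proportion correct p0 = 30-40% before and p1 = 60-90% after.

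**Chance.** A pure guesser expects 5 × 0.2 = 1.0 correct, with SD √(5 × 0.2 × 0.8) = 0.89.

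**Raw gain.** The variance of one gain is k[p0(1−p0) + p1(1−p1)]. The difference between two gains in one student has twice that. The detectable difference is (1.960 + 0.842) × SD_diff / √48 = 0.404 × SD_diff.

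| Correct before / after | SD_diff | Detectable, questions | Percentage points |
|---|---|---|---|
| 30% / 90% | √(10 × 0.30) = 1.73 | 0.70 | 14.0 |
| 30% / 70% | √(10 × 0.42) = 2.05 | 0.83 | 16.6 |
| 40% / 60% | √(10 × 0.48) = 2.19 | 0.89 | 17.7 |

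**Power for given differences in gain** (noncentral t, 48 students, SD_diff 1.6-2.2, which also covers p0 = 20%):
- 0.5 question (10 points): 34-56%
- 0.75 question (15 points): 64-89%
- 1 question (20 points): 87-99%

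The abstract's figure of fifty students changes these by at most about 2 points.

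**Post-test adjusted for pre-test.** If pre and post are uncorrelated within student, adjustment leaves only post-test noise. At p1 = 70%, SD_diff = √(2 × 5 × 0.21) = 1.45, and 0.404 × 1.45 = 0.59 question (11.7 points), against 0.83 (16.6) for the raw gain. With correlation r and p0 = 30%, p1 = 70%, the variances are 4.2(1−r) for the gain and 2.1(1−r²) for the adjusted score, a ratio of (1+r)/2. At r = 0.4 the gain detects 0.83 × √0.6 = 0.64 question (12.8 points) and the adjusted score 0.59 × √0.84 = 0.54 (10.7). The advantage narrows as r rises but does not reverse.

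**Ten items per session, raw gain.** The detectable difference is 9.9 points (30%/90%), 11.7 (30%/70%) and 12.5 (40%/60%). At 30%/70% with independent items, doubling the test and adjusting for the pre-test therefore gain the same amount. Doing both gives 8.3 points.

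**Ceiling.** The share scoring 5 of 5 afterwards is p1⁵: 8% at 60% correct, 17% at 70%, 33% at 80% and 59% at 90%. With ten items it is 11% at 80% and 35% at 90%.

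**Association.** Suppose the true between-setting learning difference varies across students with an SD of 10-20 points (an assumption). At 30%/70% the noise SD is 2.05 × 20 = 41 points. The attenuation factor is √[10²/(10² + 41²)] = 0.24 to √[20²/(20² + 41²)] = 0.44. A true correlation of 0.5 would appear as about 0.12-0.22, while 48 students detect about 0.39 at 80% power.

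**The case against.** The strongest reply is that nothing stated is wrong. The primary endpoint is SDNN, the study calls itself a pilot, it claims neither power nor equivalence for learning, and it admits that the test is unvalidated. All of this stands, and it limits the point to a recommendation.

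A reader might infer more, in three ways the article does not support.

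- **That the test cannot detect any plausible difference.** The article names no plausible difference, and a difference of one full question would be found with 87-99% power.
- **That a ceiling is built in.** Item difficulty is not given. The content is meant to be new to the students and aimed at comprehension, so post-test scores may stay moderate, and at 60-70% correct only 8-17% reach the maximum. Noise and ceiling also work at opposite ends: where the ceiling is worst, the noise is smallest.
- **That five items must be doubled.** Much of the shortfall comes from contrasting raw changes, and adjustment recovers as much as doubling in the 30%/70% case.

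Reusing the same questions is also defensible. It holds difficulty constant from pre to post, and retest effects fall on both settings. Parallel items in an unvalidated test would bring untested differences in difficulty.

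What the reply does not remove is that learning success is in the aim, and that the crossover leaves item and guessing noise within the student untouched.

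**Conclusion.** The point holds as a limit on precision, not as an error. With five items per session and a raw-gain contrast, 48 students reliably detect only about 0.70-0.89 question (14-18 percentage points). A difference of 10 points would be missed about half the time or more often. A null learning result is therefore uninformative for smaller effects, and associations with autonomic change will look weaker than they are. A ceiling is a conditional risk that becomes serious only if items prove easy after teaching, at roughly 80% correct or more.

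These figures assume independent items and the stated ranges of proportions correct. Positive correlation between pre- and post-test would reduce them (12.8 instead of 16.6 points at 30%/70% with r = 0.4). The article's wording on scoring does not fix a model, so the raw change is the natural reading rather than a declared analysis.

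**What to change.** 1. In the Learning progress test section, state that the settings are compared within student on the post-test score, adjusted for that session's pre-test score and with period in the model, instead of on the raw pre-post change. The period term matters because the two sessions appear to use different sets of five questions, whose difficulty may differ. This uses data already collected and costs nothing.

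2. Where time allows, use more items per session, for example 10. This means ten more questions per seminar, shared among three lecturers, and longer tests. The downside is the schedule: two 40-minute sessions, the 10-minute break, 3 minutes of rest and 4 minutes of baseline recording already make 97 of the roughly 100 minutes given in the Study protocol section. The extra testing time needs its own slot outside the rest break. Mixing repeated with parallel items is optional.

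3. Add to Limitations and strengths that a null learning result does not show the two settings to be equally effective, and report the difference between settings with its confidence interval.

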All subjects will be evaluated for autonomic neurocardiac, sudomotor, neurovascular and pupillomotor function as well as emotions and learning progress. Before start of a seminar and baseline measurements, a pre-test covering the content of the seminar as well as the Profile of Mood States (POMS) evaluation will be performed to assess knowledge and emotions [15]. The POMS questionnaire is a valid and widely used tool in clinical psychology to determine emotional status by measuring different dimensions of mood swings over a period of time. Subsequently, autonomic baseline measurements will be performed in which the subject will be laying comfortably in a chair with an open angel of 135 degrees. To assess neurocardiac autonomic function, a three-channel electrocardiogram (ECG) will be attached to the chest recording heart rate variability (HRV) as previously described and detailed in chapter “Neurocardiac autonomic function assessment: heart rate variability” [16]. An sympathetic skin response (SSR) electrode will be placed on the index and middle finger to assess sudomotor autonomic function, whereas an Laser Doppler Flowmetry (LDF) electrode will be placed on the ring finger to assess neurovascular function. as previously described and detailed in chapters “Sudomotor autonomic function assessment: sympathetic skin response (SSR)” and “Laser Doppler Flowmetry (LDF)” [17,18]. All electrodes will be attached to the non-dominant hand. Mobile pupillometry will be used to assess changes of pupil size and velocity. The baseline measurements of autonomic functions will last 240 s and will be undertaken after resting for 180 s prior to the start of the seminar. During each seminar session, HRV, SSR, LDF and pupillometry will be simultaneously recorded. After each interaction with the instructor, the subject will perform three deep inspirations. These breathing patterns allow separate assessment of immediate sympathetic response stimulated by deep inspiration as well as parasympathetic stimulation following metronomic breathing. All amplified and artefact-cleaned neurocardiac, sudomotor and neurovascular and signals as well as breath excursions will be converted to digital data using four-channel digitization hardware (Power-Lab 4/26®, ADInstruments, Castle Hill, Australia). The raw data will be displayed using an analysis software (LabChart Pro® 5, ADInstruments, Castle Hill, Australia). During the 10-min break between two sessions, the subject will be instructed to maintain a resting state avoiding any interaction with other classmates and the instructor. After the end of each seminar session, the subject will complete a post-test and another POMS questionnaire. Details on each assessment technique are given in the following.

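### The protocol article contradicts itself on when the learning pre-test is taken and on which score session 2 is compared with

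*Protocol article*

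**What the plan says.** The Experimental seminar section defines the unit: "One experimental seminar will be held in two consecutive phases (sessions"), one face-to-face and one by videoconference, each of 40 minutes with a 10-minute break between them. On testing it says: "A multiple-choice test will be undertaken prior and after each seminar session to assess learning progress".

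The Learning progress test section provides 10 multiple-choice questions and continues: "For each seminar session, five identical questions will be handed out to the participating subjects as pre- and post-tests". It then says: "These tests will be given to students before and after each seminar session". Its last sentence sets the comparison: "The achieved score after each seminar session will be compared with the score achieved before the seminar begins to reflect the learning success".

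The Study protocol section, in the text after Figure 1, has a different sequence. It begins: "Before start of a seminar and baseline measurements, a pre-test covering the content of the seminar", together with the mood questionnaire. Later it says: "After the end of each seminar session, the subject will complete a post-test and another POMS questionnaire". For the break it describes rest only and mentions no second pre-test. The Figure 1 caption also places topic knowledge at baseline.

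**The concern.** Two teams following this text could collect different data. One would give a pre-test before session 2. The other would give a single pre-test at the start and go from the break straight into session 2.

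The second schedule matters for what a session-2 gain means. Both sessions cover the same topic with the same instructor (Study protocol), so some learning from session 1 may help with the session-2 questions. Measured from before session 1, that learning is credited to whichever setting came second. The Introduction ends by asking whether autonomic changes in the two settings translate into differences in learning success, so the gain per session is a quantity the study intends to use.

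**Working it through.** The article gives no learning-score figure to reproduce. The check sets the statements side by side and then works out what the literal rule does.

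**Schedule**

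| Place | Pre-test | Comparator for session 2 |
|---|---|---|
| Experimental seminar | before each session | not stated |
| Learning progress test, all but the last sentence | before each session, five items | implied: the same five items |
| Learning progress test, last sentence | – | score before the seminar begins |
| Study protocol, text after Figure 1 | once, before seminar and baseline | only the pre-seminar score exists |
| Figure 1 caption | topic knowledge at baseline | not stated |

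The item count, 10 questions / 2 sessions = 5, fits a separate set for each session. This is an inference; the article does not say that the two sets differ.

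**One shared pre-test.** Let P be a single pre-seminar score used for both sessions:

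(post_F − P) − (post_V − P) = post_F − post_V.

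The pre-test drops out and adjusts nothing in the face-to-face versus videoconference contrast. If P instead covered all 10 items and were scored by subset, the items would match for each session and P would not cancel, but carry-over from session 1 would remain in the session-2 gain.

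**Carry-over.** Let g_F and g_V be the true gains within a session. Let s_F and s_V be the items that session 1 adds to the session-2 score when session 1 was face-to-face or videoconference. With the pre-seminar comparator, the contrast F − V is:

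- face-to-face first: g_F − (g_V + s_F) = (g_F − g_V) − s_F
- videoconference first: (g_F + s_V) − g_V = (g_F − g_V) + s_V
- mean over equal sequences: (g_F − g_V) + (s_V − s_F)/2

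The bias is therefore half the difference in carry-over. For assumed differences of 0.5 and 1 item it is 0.25 and 0.5 item, which is 0.25/5 = 5 and 0.5/5 = 10 percentage points on a five-item test. If s_F = s_V it is zero.

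With the same five items answered just before session 2, the carry-over sits in both pre- and post-score. It cancels from the simple gain to the extent that the pre-test captures it.

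**Illustration by simulation.** All inputs except the target of 48 subjects are assumed: 30% correct at pre-test, a gain of 30 points per session, no true difference between settings, and equal carry-over after both.

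| Carry-over (points) | Session-2 gain, pre-seminar comparator | Session-2 gain, own pre-test |
|---|---|---|
| 0 | 30 | 30 |
| 10 | 40 | 30 |
| 20 | 50 | 30 |

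With 24 subjects per sequence, the setting contrast was unbiased under either comparator. With a 30/18 split, the pre-seminar comparator shifted the unadjusted contrast by about (30 − 18)/48 = 0.25 of the carry-over, that is 2.5 or 5 points; the own pre-test shifted it by 0. The Study protocol section describes pairs with one participant starting in each setting, so such a split would depart from the stated design.

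**The case against.** The best reply is that the article uses seminar loosely. The Figure 1 caption and the section on sympathetic skin response speak of two types of seminar, meaning the two settings. The disputed sentence directly follows the statement that tests come before and after each session. It may simply mean before that session begins, which is the rule one would want. That stands: a reader might infer that the sponsor has definitely chosen the pre-seminar score for session 2, and the text does not establish it. The loose reading does not remove the conflict, however. The Study protocol section ties its only pre-test to the baseline measurements, and the heart rate variability section places the baseline rest before the first section of the seminar.

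Several stronger readings are also tempting, and the article does not support them:

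- That session 2 is scored against different questions. The Study protocol pre-test covers the seminar content, which is compatible with all 10 items and scoring by subset.
- That the setting contrast is biased in any event. Only unequal carry-over, or unbalanced sequences in an unadjusted analysis, does this.
- That unequal difficulty of the two sets inflates the standard error by a known amount. That depends on whether the pre-test is shared and on the analysis model, and the article states no model for learning scores.
- That the forms must overlap the rest period because the timed parts nearly fill the stated total. The roughly 100 minutes are described as baseline, seminar settings and break; tests and questionnaires are not listed, and nothing places them inside the 10 minutes.

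Finally, the statistical section names SDNN as primary and the remaining autonomic parameters as further endpoints, and the article discloses that this is an exploratory pilot with an unvalidated test. That limits the weight of the point.

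**Conclusion.** The contradiction is real: the sections disagree on whether a pre-test precedes session 2, and the scoring sentence read literally uses the score from before session 1 for both sessions. Under that reading, session-2 gains include whatever session 1 taught about the session-2 items, and the setting contrast is biased by about s/2 items if carry-over differs by s items between settings. The size of s is unknown and the values above are assumptions. The s/2 result also assumes equal sequences and carry-over that adds to the score. The primary endpoint is unaffected. This is a minor-to-moderate point, worth correcting because it determines which data are collected.

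**What to change.** Change the last sentence of the Learning progress test section so that each session's post-test is compared with the same five items answered immediately before that session. Align the Study protocol text and the Figure 1 caption with the Experimental seminar section. State that the session-2 pre-test is taken between the sessions, and whether it comes before or after the 10-minute rest. Whether the analysis uses simple gains or the pre-test as a covariate can be left to the analysis plan; a covariate slope below 1 would remove the carry-over only in part.

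The cost is wording and a few minutes per subject. It should be settled before enrolment, since a session-2 pre-test that was not taken cannot be recovered.
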